### Research Aims and Hypotheses

#### Quantitative Aims and Hypotheses

The primary aim is to quantitatively assess patient-reported contraceptive nonuse (yes or no) at 3 months (primary outcome).

Hypothesis 1: Contraceptive nonuse will be less likely in the intervention arm than the control arm at 3 months.

The secondary aim is to quantitatively assess the Medical Eligibility Risk category for patient-reported contraceptive method use per the US MEC schema (Category 1=no risk; Category 2=Advantages generally outweigh theoretical or proven risks; Category 3=Theoretical or proven risks usually outweigh advantages; Category 4=unacceptable health risks) [7]. Clinically translated, Categories 1 and 2 indicate methods that are safe to use, Category 3 indicates methods that should be avoided unless more appropriate methods are not available or acceptable to the patient, and Category 4 indicates methods that should be avoided [7]. We will explore the potential impact of the intervention on contraceptive decisions across US MEC categories using qualitative and mixed methods analysis, with a focus on Category 3 cases.

Hypothesis 2: Given the need for a careful and informed discussion to weigh the benefits and risks of Category 3 use, we hypothesize that the decision tool will facilitate this process, leading to more Category 3 use cases in the intervention arm than the control arm.

The exploratory aim is to quantitatively explore contraception decisional conflict measured via a modified Decisional Conflict Scale (DCS) [29], and the patient-reported quality of interaction with their contraceptive provider, as measured via the Interpersonal Quality of Family Planning Scale (IQFP) [30], as mediators of the effects of MHMC on the primary outcome.

Hypothesis 3: The impact of MHMC on contraceptive nonuse will be mediated by lower DCS scores and higher IQFP scores.

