The exploratory outcomes are hypothesized mediators of the intervention effect on the primary and secondary outcomes. First, contraceptive decisional conflict will be assessed with the DCS, a 16-item validated scale with 4 subscales [29] (0=no conflict; 100=greatest conflict). We slightly modified the wording of DCS items, when appropriate, to reflect contraceptive decisions rather than generic health decisions. Second, we will assess patient-reported quality of interaction with their contraceptive provider via the IQFP [30]. The IQFP contains 11 items that are assigned a score of 1-5 (1=poor, 2=fair, 3=good, 4=very good, and 5=excellent) by the patient to assess their clinician’s shared decision-making and interpersonal skills (total scores ranged from 11 to 55). We will conduct a mediation analysis as described by Baron and Kenny [53] with two models: (1) a logistic regression of the mediator (ie, DCS or IQFS, dichotomized) as a function of the primary outcome (contraceptive nonuse at 3 months), with a covariate for intervention versus control group, and (2) a logistic regression of the primary outcome (contraceptive nonuse at 3 months), adjusting for both the mediator (ie, DCS or IQFPS, dichotomized) and intervention versus usual care group.

We will conduct descriptive analyses on other patient, clinician, and clinic-level exploratory measures and statistical comparison tests as appropriate (eg, chi-square, Fisher exact, and *t* tests).

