## Discussion

### Principal Findings

This study aims to evaluate whether a web-based decision tool will decrease contraceptive nonuse by improving patient-reported decisional conflict and the quality of interactions with their contraceptive providers. To our knowledge, this will be the first RCT to focus on the contraception decision support needs of people with health conditions—a group at higher risk of adverse events (albeit low absolute event rates) from hormonal contraception use and pregnancy-related complications than those without health conditions [11,12]. We expect this study to advance our understanding of the impact of contraceptive decision support tools on patients’ perceptions of their clinicians’ ability to provide comprehensive information, listen to their concerns, respect patient autonomy, and engage in shared decision-making [30]. This study will also generate new knowledge regarding how patients and clinicians deliberate risk-benefit trade-offs of contraceptive use in light of ongoing health considerations.

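### Testing DCS and IQFP one at a time can credit a score that has no effect of its own if the two are correlated; Hypothesis 3 needs one model with both

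*Protocol article*

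**What the plan says.** In the protocol article, the third hypothesis (Quantitative Aims and Hypotheses) is that "The impact of MHMC on contraceptive nonuse will be mediated by lower DCS scores and higher IQFP scores". The Discussion (Principal Findings) repeats the two-part mechanism: the tool is expected to "decrease contraceptive nonuse by improving patient-reported decisional conflict and the quality of interactions with their contraceptive providers".

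The analysis is set out in Quantitative Outcomes and Analysis: "We will conduct a mediation analysis as described by Baron and Kenny [53] with two models". The first model is "a logistic regression of the mediator (ie, DCS or IQFS, dichotomized) as a function of the primary outcome (contraceptive nonuse at 3 months"; arm enters it as a further predictor. The second model is "a logistic regression of the primary outcome (contraceptive nonuse at 3 months), adjusting for both the mediator (ie, DCS or IQFPS, dichotomized"; here too arm is the other term. In both, the mediator is singular and is either DCS or IQFP. No model containing both scores is described.

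The same section gives the status of the analysis: "The exploratory outcomes are hypothesized mediators of the intervention effect on the primary and secondary outcomes".

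**The concern.** A hypothesis about two mediators is to be examined with models that each hold only one. Both scores come from the same patient and concern the same contraceptive counseling and decision, and the IQFP rates, among other things, the clinician's shared decision-making. Some within-arm correlation is therefore likely. When one correlated score is left out, the coefficient of the other absorbs part of its effect. Adjusting for arm does not prevent this, because the correlation in question is the one that remains within arm.

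At stake is the reading of Aim 3: whether the tool works through less decisional conflict, better interaction, or both. Two single-mediator analyses can point to both when only one operates, and their two mediated effects can add to more than the true total. The Limitations section also relies on these two mechanisms when it argues that the tool should work across diverse health conditions.

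**Working it through.** **1. Design figures in the article (Power and Quantitative Sample Size).** 14 clinics × 45 = 630 patients, or 315 per arm; 315 × 1.15 = 362.25, rounded up to 363; × 2 = 726, which matches the enrollment goal. With 15% lost, 363 × 0.85 = 308.55, so about 308 per arm, or 616 (14 × 44). The stated ICC is 0.05. No figure is given for the mediation analysis, so the correlation between scores, the arm shifts, the mediator effects and the cut-points below are all assumptions.

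**2. Why false credit arises.** Suppose logit P(nonuse) = c + d·arm + g·DCS, with a coefficient of 0 for IQFP. Let r be the within-arm correlation of the scores, each with unit SD. With IQFP alone next to arm, its coefficient is approximately g·r (ignoring a small logit attenuation):
- r = 0: g·r = 0, so no false credit.
- g = 0.4, r = 0.3 in size: 0.4 × 0.3 = 0.12 per SD.
- g = 0.7, r = 0.7 in size: 0.7 × 0.7 = 0.49 per SD.

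The true value is 0 throughout.

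**3. Simulation with IQFP inert.** 616 patients; arm shifts each score by 0.3 SD in the favorable direction; g = 0.4 or 0.7; r = -0.3 to -0.7. The rates below come from a run with 14 clinics and ICC 0.05.

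| Event | Share of simulated trials |
|---|---|
| IQFP significant, alone with arm, continuous | 24-99% |
| Same, dichotomized | 17-94% |
| IQFP significant, alone, r = 0 | 5-7% |
| IQFP significant, DCS also in model, both continuous | 5-9% |
| Same, both split at the median | up to 27% |
| IQFP significant alone and clinic-level arm effect on IQFP also significant | about 11-52% |

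The last row is the one closest to a declared mediation. It depends on how strongly the scores cluster: a similar run with a mediator ICC of 0.02 gave 16-68%.

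In large samples with g = 0.7, the DCS indirect effect is 3.3 percentage points. The false IQFP effect is 0.95, 1.59 and 2.27 points at r = -0.3, -0.5 and -0.7. Dividing by 3.3 gives 29%, 48% and 69%, close to |r| as step 2 implies.

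**4. Roles reversed, DCS inert.** 630 patients, 14 clinics, outcome ICC 0.05, nonuse 30% versus 10%, arm shift 0.5 SD, IQFP log-odds -0.4 to -1.0 per SD, median splits. DCS alone with arm is significant in:
- r = 0: 5-6%
- r = -0.2: 9-24%
- r = -0.4: 20-74%
- r = -0.6: 42-97%

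With both scores in the model, the rate is 3-7% for continuous scores and 4-29% for dichotomized scores. The result therefore does not hinge on which score is inert, and joint entry alone is not enough if the scores stay dichotomized.

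**5. First model as written.** It has the outcome as a predictor of the mediator, so its arm coefficient is not the effect of arm on the mediator. With a true arm effect of 0 on the mediator, the arm log-odds ratio given the outcome is 0.22 to 0.31. With a true 0.5 SD shift it is -0.55 to -0.62, instead of about -0.79. A usable indirect effect needs this model turned around as well.

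**The case against.** - **The size is assumed.** This stands. The article gives no correlation, mediator shift or mediator effect, and at zero correlation the single-mediator model behaves properly. The case is that false credit can occur, not that it must.
- **A significant mediator coefficient is not yet a mediation claim.** This stands. A claim also needs an arm effect on the mediator, judged across only 14 clinics. That brings the rate down to about 11-52%, which is still well above 5%.
- **If better interaction itself lowers decisional conflict, some credit to IQFP alone is legitimate.** This stands in part. It means that each score's separate share depends on an assumed ordering. It does not rescue the DCS-only model: if IQFP also acts directly on nonuse, that model is confounded. The joint indirect effect needs no choice of which score comes first.
- **Hypothesis 3 does not ask for the effect to be divided between the scores.** True, but it names both as carrying the effect, and no stated model estimates what the two carry between them.
- **The estimator belongs to the analysis plan.** A reader might infer that no mediated effect will ever be estimated, or that mediation will be judged from separate P values. The article supports neither. It names a mediation method and states no decision rule, and a condensed article commonly leaves the indirect-effect step and its interval to the analysis plan. What the article does fix is the content of the two models, and the point rests on that.
- **The aim is exploratory.** Agreed, and this limits the weight of the point.

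**Conclusion.** The point holds in conditional form. The stated models enter DCS and IQFP one at a time although Hypothesis 3 names both, so if the scores are correlated within arm, one with no effect of its own can be credited with the other's. With assumed correlations of 0.3 to 0.7 in size, arm shifts of 0.3 SD and a mediator log-odds ratio of 0.4 to 0.7 per SD, the size is as tabulated: a spurious outcome-model finding is common, and a spurious mediation finding is several times more frequent than the nominal level over most of the range.

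Two further readings go too far. A reader might infer that an inert score will always be credited; the zero-correlation result contradicts that. A reader might also infer that the trial's main conclusion is at risk; the primary comparison and the enrollment goal do not use these models and are unaffected. This is a worthwhile and inexpensive correction to an exploratory analysis.

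**What to change.** For this exploratory aim, in the analysis plan:

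1. Fit one model of 3-month nonuse on arm, DCS and IQFP together, with both scores kept continuous.
2. Pair it with a model of each mediator on arm, without the outcome on the right-hand side.
3. Report the joint indirect effect through both scores, with an interval that respects clinic clustering, as the main result for Hypothesis 3.
4. Report each mediator's separate contribution as secondary and state the assumed ordering of the two scores. Single-mediator results may stay as supportive.

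The cost is wording and modest programming; no new data are needed. The downside is that the separate contributions are less precise when the scores are highly correlated, and they depend on the ordering assumption.

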### Patient Study Activities and Quantitative Data Collection

Enrolled patients will complete an electronic baseline survey to report demographics, health history, past and current contraceptive use, contraceptive knowledge, and the secondary and exploratory outcomes (see “Quantitative Outcomes and Analysis” section). To mitigate the risk of differential dropout, recruitment bias, or bias in baseline assessments, we will inform participants of their clinic group assignment after their consent and baseline surveys have been completed [39]. Although this approach entails temporary withholding of information, it is consistent with the Ottawa Statement on the Ethical Design and Conduct of Cluster Randomized Trials [39].

Patients in both the intervention and control arms will receive a web link to a brief video that explains “What to Expect” regarding study activities. Only those in the intervention arm will receive web links to the MHMC tool, a brief video that reviews how to log in and navigate the tool’s features, and a posttool survey to report their experience using MHMC.

The study team will encourage all patients to attend their upcoming clinic visit. Immediately after the clinic visit, patients will receive a postvisit survey and be asked to complete this within 5 days. They will be asked to complete surveys 1 month and 3 months after the clinic visit. Patient surveys require 5-15 minutes to complete. The study team will invite approximately 30 patients who complete study participation to do an optional 1-hour qualitative exit interview by phone or videoconference (refer to “Qualitative Data Collection and Sampling Considerations” section). Patients will receive up to US $100 in cash remuneration for completion of study activities (Figure 4).

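### Dichotomizing the DCS and IQFP in the mediation models leaves part of a truly mediated effect on the arm term, and does not match a hypothesis stated in scores

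*Protocol article*

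**What the plan says.** Hypothesis 3 (Quantitative Aims and Hypotheses) reads "The impact of MHMC on contraceptive nonuse will be mediated by lower DCS scores and higher IQFP scores". The section Quantitative Outcomes and Analysis presents both instruments as graded: the DCS with "0=no conflict; 100=greatest conflict", and the IQFP as 11 items scored 1 to 5 ("total scores ranged from 11 to 55").

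The same section continues: "We will conduct a mediation analysis as described by Baron and Kenny [53] with two models". The first is "a logistic regression of the mediator (ie, DCS or IQFS, dichotomized) as a function of the primary outcome", with a covariate for arm. The second is a logistic regression of 3-month nonuse, "adjusting for both the mediator (ie, DCS or IQFPS, dichotomized) and intervention versus usual care group". So the yes/no coding is stated for both models. The article gives no reason for it and mentions no analysis of the continuous scores.

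The aim is labelled exploratory: "The exploratory outcomes are hypothesized mediators of the intervention effect on the primary and secondary outcomes".

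**The concern.** The second model is meant to show how much of the arm effect on nonuse remains once the mediator is held constant. A yes/no version does not hold it constant. Among patients on the same side of the cut, those in the intervention arm can still have lower conflict or better interaction quality. If nonuse depends on the score in a graded way, that remaining difference goes into the arm coefficient and looks like an effect of the tool outside the mediator. This is bias rather than noise, so more patients would not remove it.

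Cutting the scores also weakens the comparison of arms on each scale, which is the other link in the mediation argument.

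The mechanism matters to this trial. The Principal Findings section describes the study as testing whether the tool works through decisional conflict and interaction quality. The Limitations section relies on the same mechanisms to defend pooling many health conditions.

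**Working it through.** The article gives no figure for the mediation analysis, so there is none to reproduce. From the Power and Quantitative Sample Size section come 45 patients per clinic, 7 clinics per arm, an ICC of 0.05 (stated for nonuse) and a 20% difference in nonuse, read here as 20 percentage points. Everything else below is assumed.

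**1. Effect left on the arm term under full mediation.** Let the score be M = -a × arm + N(0,1), and logit P(nonuse) = c + b × M. Arm affects nonuse only through M, so the correct direct effect is 0. Fit nonuse on arm plus M, first continuous and then cut.

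- *Small effect*: a = 0.4, b = 0.7, c = -1.2, giving nonuse of about 25% vs 21%.
- *Planned-size effect*: a = 1.02, b = 1.0, c = 0, giving 50% vs 30%. The total is logit(0.30) - logit(0.50) = -0.847.

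| Log-odds arm effect | Small effect | Planned-size effect |
|---|---|---|
| Total | -0.258 | -0.847 |
| Adjusted for continuous score | 0 | 0 |
| Adjusted for median cut | -0.098 (38%) | -0.319 (38%) |
| Adjusted for cut at 80th percentile | -0.120 (47%) | -0.481 (57%) |
| Adjusted for cut at 20th percentile | -0.156 (60%) | -0.534 (63%) |

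The share is the adjusted effect divided by the total, for example 0.098/0.258 = 0.38. Logistic coefficients shift with the covariates in the model, so the shares were also computed as risk differences over a grid of shifts (0.3 to 0.8 SD) and slopes (0.5 to 1.5) with nonuse near 30%. They were 33-38% at a median cut and 40-50% at the 80th percentile. At the planned-size effect, a steeper slope of 2.0 raises the log-odds shares slightly, to 40% at the median and 59-68% at 80/20, so the figures are not bounds.

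**2. When the bias disappears.** If the true relation is a step exactly at the chosen cut, the dichotomized model leaves 0.0005 of a total of -0.280, which is essentially nothing.

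**3. Information in the arm comparison, independent patients.** For a normal score cut at quantile q, the fraction retained is r = φ(z_q)² / [q(1-q)].

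- Median: r = 0.637, loss 36%
- 80/20: r = 0.490, loss 51%
- 90/10: r = 0.342, loss 66%

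**4. The same with clustering.** Cutting a score also lowers its ICC. With 45 per clinic the design effect is 1 + 44 × ICC. If the scale has ICC 0.05, that is 1 + 44 × 0.05 = 3.20 for the continuous score. The ICC of the cut score follows from the bivariate normal; at the median it is (2/π) × arcsin(0.05) = 0.0318. Relative efficiency is r × 3.20 / (design effect of the cut score).

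| Cut | ICC after cut | Design effect | Relative efficiency | Loss |
|---|---|---|---|---|
| Median | 0.0318 | 2.401 | 0.637 × 3.20/2.401 = 0.85 | 15% |
| 80/20 | 0.0249 | 2.097 | 0.490 × 3.20/2.097 = 0.75 | 25% |
| 90/10 | 0.0178 | 1.784 | 0.342 × 3.20/1.784 = 0.61 | 39% |

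With a scale ICC of 0.02 the losses are 23%, 36% and 51%.

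**5. Non-normal scores.** For a simulated 11-item, 1-to-5 score with a ceiling, the loss for independent patients ran from about 30% to 87%, depending on cut and skew.

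**The case against.** Several points against this stand and limit what can be claimed.

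- *Size.* A reader might take 36-66% as the information this trial would lose. The documents do not support that: it assumes a normal score, cuts between the median and 90/10, and independent patients. In a simulated comparison of 7 vs 7 clinic means with a 0.4 SD shift and ICC 0.05, power fell from 73% to 67% at a median cut, 60% at 80/20 and 50% at 90/10. The loss is real but moderate for a central cut.
- *Extent of the bias.* A reader might infer that mediation would look wholly direct. Only part is misattributed; at a median cut most of the mediated effect is still recovered.
- *Consequence.* A reader might infer that Hypothesis 3 would be declared false. It does not claim complete mediation through one scale. The models appear to take the DCS and IQFP one at a time, so an arm effect acting through the other scale would remain even with perfect measurement.
- *Omissions.* The article gives no cut-point and does not mention adjusting for baseline DCS, although the baseline survey collects "contraceptive knowledge, and the secondary and exploratory outcomes". An article may leave both to the full plan; neither is part of this point.
- *Status.* The aim is exploratory.

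None of this removes the core. Dichotomizing is a stated choice, not a missing detail. Nothing in the article posits a threshold, and the hypothesis is worded in scores.

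**Conclusion.** The point holds in a limited form. Both mediation models cut graded scales to yes/no although the hypothesis concerns scores. With a graded relation, part of a mediated effect then appears as a direct effect of the tool: about 38% at a median cut and 47-63% at an 80/20 cut, against about 0 with the continuous score. This assumes a normal score and full mediation through that one scale, and it would vanish only if the true effect were a step at the cut. The accompanying loss in the arm comparison is about 15-39% under the clustered assumptions, and 36-66% only if patients were independent.

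The bias understates mediation. It does not by itself refute Hypothesis 3, and it does not reach the primary analysis or the sample size. It is worth correcting because it affects the trial's account of how the tool works and costs almost nothing to remove.

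**What to change.** In Quantitative Outcomes and Analysis, replace the dichotomized mediators with the continuous total DCS (0-100) and IQFP (11-55) scores in both models. Where the score is the dependent variable, use a linear mixed model that keeps the clinic clustering. In the nonuse model, enter the continuous score together with arm. Keep any dichotomy as a sensitivity or descriptive analysis.

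The cost is a wording change, with no new data. If the IQFP shows a ceiling, a linear model fits it less well, and a small ordinal or rank-based sensitivity check should be added. Adjusting the DCS models for baseline DCS is optional. The first model as written places the mediator as a function of the outcome; that direction is a separate matter, and correcting it alone would leave this bias in the second model.

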## Methods

### Trial Design and Rationale: A Cluster RCT With a Mixed Methods Design

This study protocol reflects the SPIRIT (Standard Protocol Items: Recommendations for Intervention Trials) 2025 checklist for reporting RCTs [31]. For this efficacy trial, we will conduct a 2-arm, parallel cluster RCT using mixed methods to compare MHMC and usual care (intervention arm) to usual contraceptive care (control arm) in outpatient primary care or obstetrics and gynecology clinics in the United States. We will randomize at the level of the clinic site (the cluster unit) rather than the individual patient [32]. This group-level randomization approach prevents clinicians from influencing each other’s contraceptive practices or changing their contraceptive practices after exposure to MHMC, which then impacts the treatment of subsequent patients [32]. The rationale for incorporating qualitative methods and mixed methods (the integration of quantitative data and qualitative data) in this RCT is to more deeply understand how patients and providers navigate contraceptive decisions in the context of health conditions [33]. In particular, we seek to focus on challenging cases in which there is a method that should be avoided except in special circumstances when there is no appropriate or patient-acceptable alternative. We will use an explanatory sequential design [34], in which qualitative exit interviews will be done after survey data collection to explain our quantitative findings. Figure 1 depicts the mixed methods RCT design and the activities of each data collection and analysis phase.

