### Quantitative Outcomes and Analysis

The primary outcome is contraceptive nonuse at 3 months per patient self-report, consistent with prior contraceptive studies [10,51,52]. Individual contraceptive nonuse will be modeled as a binary outcome. We will use mixed-effects nested logistic regression to assess differences in 3-month outcomes between the study arms. The model will include an arm assignment categorical covariate and will be adjusted using patient-level covariates (baseline contraceptive nonuse, education, race, ethnicity, and parity) and clinician-level covariates (self-reported experience with contraceptive care and specialty type). Random intercepts for the clinic and for clinicians nested within the clinic will account for the clustering. Secondary analyses of contraceptive nonuse will include the same model with 1-month data and a subgroup analysis that only includes patients at risk for pregnancy, that is, those who report penile-vaginal sexual activity at 1 month and 3 months.

The secondary quantitative outcome is patient-reported contraceptive method use as classified by the US MEC. We will summarize US MEC Categories 1, 2, 3, or 4 among patients who report contraceptive use at 1 month and at 3 months with descriptive statistics. Chi-square tests will be calculated to compare frequencies between the intervention group and the usual care group.

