Patient-level measures: We will categorize patient-reported contraceptive use by method type and method effectiveness (highly effective, moderately effective, and less effective) to enable comparison with other studies. Patients will be asked to assess 6 knowledge questions regarding contraceptive safety (true, false, or I don’t know) at baseline, postdecision tool use (for intervention arm only), and postclinic visit. Patients will be instructed to report any pregnancies that occur during the study and at 1 month and 3 months. For any pregnancies reported, patients will be asked to describe their pregnancy intentions at the time of pregnancy using a standardized single item [54]. Patients who are still pregnant at the time of reporting will exit the study and seek follow-up care; they may contribute data up until the point of study exit.Clinician-level measures: We will assess clinician knowledge of the US MEC Guidelines at baseline and exit surveys with 5-point Likert-scale items regarding 4 clinical scenarios.Clinic-level outcomes: RE-AIM is an evaluation framework to assess an intervention’s potential to be translated to real-world settings [35]. We will assess each dimension of RE-AIM with quantitative data, qualitative data, or both:Reach: We will collect demographics of participants offered the intervention and those who used the intervention, and these will be compared with those of the usual contraceptive care arm, as well as the general US population at risk for unplanned pregnancy (quantitative).Efficacy: We will examine the primary outcome of contraceptive nonuse (quantitative) in the context of patient and clinician perspectives on the intervention’s impact (qualitative).Adoption: We will report the percentage of patients and clinicians in the intervention arm who used the decision tool intervention.Implementation: We will report patient and clinician fidelity to the intervention and what natural adaptations were made (quantitative and qualitative).Maintenance: We will summarize patient- and clinician-reported facilitators, barriers, and suggested changes to sustain use of the intervention in clinical practice beyond the clinical trial (qualitative).

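### The tests named for the exploratory between-arm comparisons ignore the randomized clinic, so knowledge comparisons made with them would reject too often (minor)

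*Protocol article*

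**What the plan says.** On design, under *Trial Design and Rationale*: "We will randomize at the level of the clinic site (the cluster unit) rather than the individual patient".

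On the measures, under *Quantitative Outcomes and Analysis*:
- Patients: "Patients will be asked to assess 6 knowledge questions regarding contraceptive safety", and this happens "at baseline, postdecision tool use (for intervention arm only), and postclinic visit". Both arms therefore have a baseline and a postvisit value.
- Clinicians: "We will assess clinician knowledge of the US MEC Guidelines at baseline and exit surveys with 5-point Likert-scale items regarding 4 clinical scenarios".

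On the analysis of these and the other exploratory measures, the same section plans descriptive analyses on "other patient, clinician, and clinic-level exploratory measures and statistical comparison tests as appropriate (eg, chi-square, Fisher exact", with t tests closing the list. The list is introduced as examples. Knowledge is not named in that sentence, and the t tests are not described as paired, two-sample or on change scores.

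The primary model is treated differently: "Random intercepts for the clinic and for clinicians nested within the clinic will account for the clustering". That model also adjusts for baseline nonuse. The same model is carried to the 1-month data and to a subgroup analysis of nonuse. No clustered or baseline-adjusted method is named for knowledge.

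**The concern.** When whole clinics are randomized, people in one clinic tend to resemble each other, and the arm comparison has only 14 independent units. A chi-square, Fisher exact or ordinary t test counts each patient or clinician as independent. The standard error is then too small and the P value too low.

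Knowledge bears directly on the trial's rationale. The Introduction notes that earlier decision-tool trials did not address what clinicians know about contraception for patients with health conditions, and it expects this tool to meet the information needs of both patients and clinicians. An apparent gain in knowledge would be an attractive result to report. With the named tests, such a gain could appear by chance more often than the nominal level suggests.

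**Working it through.** **Inputs, all from *Power and Quantitative Sample Size***
- 14 clinics, 7 per arm, 45 patients per clinic.
- 5 to 10 clinicians per clinic, so 14 × 5 = 70 to 14 × 10 = 140.
- ICC 0.05 (planning value) and 0.02 (an earlier trial of a contraceptive decision tool). The article uses both to plan the nonuse comparison.

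**Assumptions.** Two-sided 5% tests, and ICCs of the same size for knowledge. The article states neither.

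**The plan's own figure.** No sample size is given for knowledge. The enrollment goal reproduces: 7 × 45 = 315 per arm; 315 × 1.15 = 362.25, rounded up to 363; 2 × 363 = 726. So 45 per clinic is the size after attrition.

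**Formula.** With m people per clinic, the design effect is DE = 1 + (m − 1) × ICC. A nominal 5% test that ignores the clinic has true two-sided error of about 2 × [1 − Φ(1.96/√DE)].

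| Measure | m | ICC | DE | True error |
|---|---|---|---|---|
| Patient knowledge | 45 | 0.02 | 1 + 44 × 0.02 = 1.88 | 15.3% |
| Patient knowledge | 45 | 0.05 | 1 + 44 × 0.05 = 3.20 | 27.3% |
| Clinician knowledge | 5 | 0.02 | 1 + 4 × 0.02 = 1.08 | 5.9% |
| Clinician knowledge | 10 | 0.02 | 1 + 9 × 0.02 = 1.18 | 7.1% |
| Clinician knowledge | 5 | 0.05 | 1 + 4 × 0.05 = 1.20 | 7.4% |
| Clinician knowledge | 10 | 0.05 | 1 + 9 × 0.05 = 1.45 | 10.4% |

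If almost nobody is lost by the postvisit survey, m approaches 726/14 ≈ 52. At ICC 0.05, DE is then 1 + 51 × 0.05 = 3.55 and the error is 29.8%.

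**Does using the baseline score help?** A simulation (7 clinics per arm, 3,000 runs per setting, baseline-to-follow-up correlation r of 0.3, 0.5 and 0.7, all assumed) gave these results for 45 per clinic and ICC 0.05:
- t test on the follow-up score: 25% to 27%.
- t test on the change score: 26% to 27%.
- Individual-level regression on arm and baseline, without clinic: 26% to 29%.
- Clinic-level, baseline-adjusted t test with 14 − 2 = 12 degrees of freedom: about 4.5% to 5.5%. It stayed between 4.3% and 6.1% in all settings, including clinics of 5 and 10.

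The simulation gave clinic and individual effects the same r, so change scores kept the same ICC. More stable clinic effects would make the excess smaller. For example, take clinic-level correlation 0.9 and individual-level correlation 0.5 (both assumed). The change-score ICC is 0.05 × 0.2/(0.05 × 0.2 + 0.95 × 1.0) ≈ 0.010, DE is about 1.46, and the error is still about 10%.

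**Precision from the baseline score.** Variance falls by about r²: 9% at r = 0.3, 25% at r = 0.5. In simulation the adjusted variance was 0.90 to 0.94 of the unadjusted variance at r = 0.3, and 0.74 to 0.76 at r = 0.5.

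**The case against.** The list of tests is open, is limited to what is appropriate, and does not mention knowledge. A condensed article may leave the model for an exploratory measure to an analysis plan that is not shown. None of the three hypotheses concerns knowledge, and the primary model shows that the team knows about clustering.

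Much of this stands, and it sets the severity. It does not remove the point, because the article does name methods, and every example assumes independent observations. The same section compares the secondary outcome (medical eligibility categories) between arms with plain chi-square tests, directly after specifying a mixed model for nonuse. That supports a literal reading of the exploratory list.

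Three stronger readings are tempting, and the documents support none of them:
- A reader might infer that the plan commits to two-sample tests that discard the baseline score. The text says only t tests, and a paired or change-score t test would use the baseline.
- A reader might infer a large loss of precision. The article gives no correlation between baseline and follow-up, and at r = 0.3 the loss is only about 9%.
- A reader might take clinician knowledge as the sole check on the clinician side of the tool. The article also plans the patient-rated interpersonal quality scale, a clinician survey after each enrolled visit, adoption and fidelity measures, and clinician interviews.

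**Conclusion.** The point holds for clustering. Used as named, the tests would give true error of about 15% to 27% for patient knowledge and about 6% to 10% for clinician knowledge. The clinician excess is modest and, at ICC 0.02, close to nominal. These figures rest on two-sided 5% testing, on carrying the nonuse ICCs over to knowledge, and on the planned clinic sizes. A paired or change-score version does not remove the problem, though it could lessen it if clinic effects are stable over time. Failure to use the baseline score is not established by the text; baseline adjustment is a secondary improvement. The aims, hypotheses and primary analysis are untouched. Severity: minor.

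**What to change.** For between-arm comparisons of patient knowledge (postvisit) and clinician knowledge of the eligibility guidelines (exit), replace the named tests with a mixed model of the follow-up score on arm and baseline score. Include a clinic random intercept, plus clinician within clinic for patient measures as in the primary model, and base inference on clinic-level degrees of freedom (about 12). A clinic-level analysis of baseline-adjusted means is an acceptable and simpler alternative. If items are analysed singly and not as a score, keep the same structure with a logistic or ordinal model. State also that any other exploratory between-arm test will account for clinic. Purely descriptive summaries need no change.

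The cost is a few lines of wording. Both baseline scores are already planned, so no new data are needed. P values will be less favourable than those from the named tests.
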